## Discussion

The study aims to measure the effectiveness of consuming Fe-fortified lentils on the body Fe status and cognitive performance in adolescent girls. Cooked Fe-fortified lentil (dal) is the only intervention considered in this study. To measure its effectiveness, we controlled other covariates that may have influence over the study outcomes: we are providing non-Fe-fortified lentils; cooked rice is being provided to increase compliance (based on the previous pilot study findings); and participants are being dewormed by albendazole at the time of feeding trial [31–33].

Adolescent girls are prone to Fe deficiency, particularly in resource-poor settings, due to a variety of factors. Although this study is limiting participation to adolescent girls, we will serve the Fe-fortified lentil to all children and teens who are participants in the BRAC Adolescent Club during the intervention period for the purposes of equity. Adolescents who do not meet the inclusion criteria, however, will not be included in the analyses. Spill-over effect is less likely to occur as the study does not provide knowledge or any other information that may affect the study outcomes, which are biological in nature.

Another aspect that may affect our outcomes is that as the study proposes to serve the same recipe for ~ 4 months, it is possible that consumption of a single recipe daily for this length of time could lead to boredom among participants and may reduce consumption or may result in drop-outs after several weeks. We predicted this situation would occur and attempted to address it in our pilot study in 2016–2017, which ran for 3 months and tested two different recipes (a thick and a thin preparation) given in three different amounts, using local ingredients and cooking procedures. This study came up with a single recipe that was found to be most acceptable to the participants (BRAC Adolescent Clubs in nearby Gazipur district), and we did not have drop-outs or reduced consumption due to palatability. Furthermore, it is important for the study to maintain its rigor and standardize the intervention recipe in order to capture the true effect of the Fe-fortified lentils compared to normal lentils and/or usual intake. So, the probability of any fluctuation in the feeding trial due to the recipe would equally affect each intervention arm, provided that we use the same recipe for the duration of the study among all arms. If we provided different recipes to increase the consumption, it is possible that the study participants would increase or decrease their consumption compared to the earlier recipe (even though the probability of fluctuation remains the same), and that could cause variation in the study outcome.

Quality control will be ensured by following multiple steps. For instance, direct training of enumerators, data quality control supervisors, and data managers will be carried out prior to the commencement of data collection to ensure equal adherence to the consent, assent, and questionnaire with the same degree of questioning and accurate understanding of the format. Furthermore, in this face-to-face interview approach using a close-ended questionnaire, response options will be strictly formatted. Field enumerators will be advised to cross-check the questionnaire among team members before sending it to the server using a cellular Internet data connection. Additional training will be provided to the data quality control supervisors at the field level, and the interview process will be spot-checked in order to uncover any mistakes in the data collection procedures.

All interviews and arthrometric measurements will be performed separately by experienced female interviewers in a private setting in the presence of a witness. Each arthrometric measurement will be taken three times to ensure consistency. Survey and daily data will be collected electronically by the Open Data Kit (ODK) app on an Android-based platform [39, 40]. This customizable mobile or tablet-based app can work both online and offline allowing the use of GPS tracking, setting the condition of the responses and enabling real-time data monitoring. An experienced data manager will be thoroughly checking the data received every day and will be providing feedback directly to the enumerators. Additionally, our data manager will be assessing the need for re-training the field staff.

The benefits of this study are threefold. First, the results of the study will be used to garner support and substantiate large-scale market expansion of Fe-fortified lentils in Bangladesh and in other countries where lentils are consumed as a staple. Second, the extensive BRAC country-wide program network has high potential for efficient marketing of high-Fe lentils throughout Bangladesh. Third, the results from this study will contribute to the knowledge on food-based approaches to enhancing the Fe status of adolescents worldwide in resource-poor settings.

Compared to the effect of Fe supplementation to improve Fe status, we expect a smaller effect size in this study. The study will require a greater number of samples to statistically detect the smaller differences between baseline, midline and endline, and between-groups status in mean sFer. The small increase in mean ferritin status has the potential to reduce the prevalence of Fe deficiency by shifting a certain proportion of the deficient population above the cutoff level (sFer > 12 μg/L). Considering the prevalence of Fe deficiency (sFer < 12 μg/L) of ~ 30% among female adolescents in rural areas, shifting the population mean sFer from 22.5 μg/L to 27.5 μg/L would reduce the prevalence to about 20%.

Three different platforms will be used for dissemination of the study results. The study findings will be presented at academic seminars at the University of Saskatchewan. Furthermore, the same results will be presented in a seminar that will be organized by the BRAC Research and Evaluation Division. A layperson’s summary of the results will be shared with BRAC for dissemination at the field level. The study findings will be presented at various conferences, such as the American Society for Nutrition (ASN), Canadian Society for Nutrition (CSN), University of Saskatchewan annual Life and Health Science Expo, and other nutrition and public health conferences. Manuscripts will be written based on the study findings and submitted to high-impact factor, peer-reviewed scientific journals Additional file 1.

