## Trial objectives

The primary objective of the study is to determine the effectiveness of an Fe-fortified lentil-based dietary intervention compared to ordinary lentils and usual intake group in improving the Fe status of non-pregnant adolescent girls in Bangladesh. The primary comparison would be Fe-fortified lentils versus non-Fe-fortified lentils and the secondary comparison would be Fe-fortified lentils versus usual intake. We hypothesize that the supplemental food-based Fe from the fortified lentils will improve body Fe status in adolescent girls, and thus cognitive performance, compared to ordinary lentils and usual intake. Furthermore, we will examine the effect of Fe-fortified and non-Fe-fortified Canadian lentil consumption (intervention) on growth (height, body weight, triceps skinfolds, mid-upper arm circumference) of non-pregnant adolescent girls in Bangladesh.

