### Intervention

There will be three arms in this effectiveness trial. Arm 1 will receive Fe-fortified lentils, arm 2 will receive unfortified lentils, and arm 3 will receive no intervention i.e. no additional lentil (usual intake group) and will serve as a control group. The usual intake group will serve as control for the lentil-related research questions, but not those pertaining to the fortification itself. Participants will not be asked to change anything about their food intake during the study, including lentil intake. Participating adolescents will be served a thick preparation of cooked lentils (37.5 g raw lentil) 5 days per week for 85 feeding days (around 4 months).

A team of 3 will manage the distribution of the lentil preparation: (1) a locally-recruited cook, (2) a research assistant who will measure and serve the cooked lentils, and (3) an Adolescent Club leader who will assist in serving and ensuring that safe drinking water is available. A locally acceptable, standard lentil dal recipe identified during the earlier feasibility study will be used. The recipe for thick cooked lentils will include turmeric 5 g, chopped onion 40 g, garlic 8 g, green chili 3 g, water 700 ml, salt 1.5 teaspoon, soybean oil 10 teaspoons, and one small bay leaf (*tejpata*) per 100 g uncooked lentils. The average cooking time would be around 18 min, and the approximate weight (after cooking of 37.5 g raw lentil) would be approximately 200 g [15]. All adolescent boys and girls who attend the BRAC Adolescent Clubs will be offered the cooked lentils during the period of the intervention; however, the information on those girls not meeting the inclusion criteria will not be analyzed.

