The simple reaction time (SRT) task provides an estimate of the speed of the simplest possible behavioral response to a visual stimulus and requires a participant to press a button in response to the onset of the task stimulus [26]. The go/no-go (GNG) task provides an estimate of the efficiency of sustained attention and the speed of simple attentional capture without the need to filter information from any immediately competing stimuli [26]. It requires a participant to press a button in response to the presentation of an infrequent stimulus (presented on 20% of the trials) and to withhold a response to a frequent stimulus (presented on 80% of the trials). The attentional network task (ANT) is a modified flanker task that provides an estimate of the effectiveness of three distinct components of attention [27]. In each trial, a participant will be presented with either an informative or an uninformative cue and will be required to press a button to indicate whether an arrow in the center pointed to the left or right while attempting to disregard flanking elements. The cued recognition task (CRT) is a modified version of a classic, visual recognition, memory task that estimates the speed, accuracy, and efficiency of recognition based on short-duration visual memory [28, 29]. Participants will be presented with a set of pictures of common, easily named objects, after which an equal number of previously seen and new items will be presented, and participants will be required to indicate whether each item was in the original set or is new. The Sternberg memory search (SMS) task estimates the speed and accuracy with which immediate visual memory can be searched [30]. In each trial, participants will be first shown a set of 1, 3, or 6 simple graphical symbols to remember, then a test stimulus will be presented, and the participant will indicate whether she remembers the test stimulus from the previous set of symbols. It would take around 45 min per participant.

Data on how much cooked lentil was served to each adolescent girl and how much remained uneaten by each girl will be collected on a daily basis by the research assistants. This information will be used to determine the actual amount of cooked lentil consumed by the adolescents.

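### Cooked rice is provided but left out of the declared intervention, so contrasts with usual intake very probably measure a dal-and-rice meal and not lentils alone

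*Protocol article*

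**What the plan says.** All references are to the protocol article.

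- **Discussion.** The trial's scope is put as "Cooked Fe-fortified lentil (dal) is the only intervention considered in this study". The following sentence lists measures taken to control other influences on the outcomes, among them that "cooked rice is being provided to increase compliance (based on the previous pilot study findings".
- **Intervention.** The section gives the serving team, recipe, portion and schedule: "Participating adolescents will be served a thick preparation of cooked lentils (37.5 g raw lentil) 5 days per week for 85 feeding days". Rice is not mentioned. The third arm is described thus: "arm 3 will receive no intervention i.e. no additional lentil (usual intake group) and will serve as a control group". Its role is limited: "The usual intake group will serve as control for the lentil-related research questions, but not those pertaining to the fortification itself". Background diet is left alone: "Participants will not be asked to change anything about their food intake during the study, including lentil intake".
- **Trial objectives.** Fortified against unfortified lentils is the primary comparison and fortified lentils against usual intake the secondary one. The hypothesis credits iron from fortified lentils with a benefit over both comparators. On growth, "we will examine the effect of Fe-fortified and non-Fe-fortified Canadian lentil consumption (intervention) on growth".
- **Data collection tools and technique.** Research assistants record the cooked lentil served and left uneaten each day. The stated use is: "This information will be used to determine the actual amount of cooked lentil consumed by the adolescents". Rice is not mentioned.
- **Discussion, on the single recipe.** Standardising the recipe is said to let the trial capture the true effect of fortified lentils against normal lentils, usual intake, or both.

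**The concern.** A food that the trial itself provides so that participants will eat the study food is a co-intervention. It is controlled for a given contrast only if both arms in that contrast receive it equally. The article calls dal the sole intervention, reports a second food, and treats that food as a controlled covariate without saying who gets it.

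What is at stake is attribution in the usual-intake contrasts. Growth, one of the two key secondary outcomes in Table 1 (the other is hemoglobin), includes body weight, arm circumference and skinfolds, which plausibly respond to extra food of any kind. Cognition is listed there as a primary outcome and might respond to a regular meal. A favourable difference from usual intake could be reported as an effect of lentils, or of their iron, when the rice contributed to it. The results are meant to support large-scale market expansion of fortified lentils, so the label on the effect matters.

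**Working it through.** The plan states no figure to reproduce here. The check is to set out what each arm receives and see what each contrast can identify.

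**Inputs**

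| Component | Arm 1 | Arm 2 | Arm 3 | Source |
|---|---|---|---|---|
| Fortificant iron (F) | yes | no | no | Intervention |
| Dal dish from 37.5 g raw lentil, staff-served, 5 days per week, 85 feeding days (D) | yes | yes | no | Intervention |
| Cooked rice (R) | very probably | very probably | very probably not | Discussion; arms and amount not stated |

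Duration: 85 feeding days / 5 per week = 17 weeks.

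**Which arms get rice.** There are two readings.

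1. *Rice only in the lentil arms.* This fits the stated purpose, since compliance has meaning only where dal is served. It also fits arm 3 receiving no intervention.
2. *Rice in all three arms.* Arm 3 would then receive a trial-provided food, against the Intervention section, and would no longer be on usual intake.

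Reading 1 is much the more likely, but it is an inference. Under either reading the Intervention section and the Discussion do not agree.

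**What each contrast contains under reading 1** (additive shorthand, ignoring interactions and displaced home food; R1 and R2 are the rice in arms 1 and 2)

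- Arm 1 − arm 2 = (F + D + R1) − (D + R2) = F + (R1 − R2). This equals F when R1 = R2.
- Arm 1 − arm 3 = F + D + R1.
- Arm 2 − arm 3 = D + R2.

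Of the three pairwise contrasts, one isolates fortification if rice is equal. The other two carry the full rice term. No contrast gives D alone, and no arm receives rice without dal, so the design cannot separate them.

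**Where the affected contrasts are used.** Arm 1 − arm 3 is the secondary comparison in Trial objectives. Both usual-intake contrasts serve the growth question there and the lentil questions that the Intervention section assigns to arm 3.

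**Size of R.** The article gives no portion, so no energy or nutrient figure can be derived, and none is assumed here.

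**The case against.** The strongest reply is that the main question is intact. The primary comparison is between two lentil arms with the same recipe, and nothing suggests that their rice differs. For that comparison, providing rice equally is legitimate balancing. This stands, on condition that the portions are equal, which the article does not say.

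Second, the Intervention section already excludes arm 3 as the control for fortification questions. This stands too, and it covers half of the relabelling. It does not cover the lentil questions, and Trial objectives still sets fortified lentils against usual intake and credits iron.

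Third, an article condenses, so rice portions and log forms may be in the full protocol. That is fair for the detail. It does not remove the conflict between calling dal the only intervention and reporting a second food. The food frequency questionnaires at baseline and end of study give some dietary information, but they do not replace a daily record of rice at the club.

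Several stronger readings are tempting and are not supported:

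- *That the primary comparison is confounded.* No text points to unequal rice.
- *That the cooking oil also contradicts the sole-intervention statement.* Oil is part of the dal recipe (10 teaspoons per 100 g raw lentil, so 10 × 37.5/100 = 3.75 per portion) and hence of the declared intervention. Energy figures built on it would not measure the rice or a net difference between arms, since displaced home food is unknown.
- *That rice is known to be unweighed.* The article describes a lentil record and is silent on rice.
- *That feeding raises club attendance.* All arms are existing clubs with afternoon activities, and no change in attendance is described.
- *That deworming differs by arm.* It is described for participants generally.

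**Conclusion.** The concern holds in a limited form. The Discussion contradicts itself and does not match the Intervention section on whether dal is the only thing provided. Given the strong but unstated inference that rice goes only to the lentil arms, both usual-intake contrasts estimate the effect of a served dal-and-rice meal against no meal. That is a valid package effect; only its attribution to lentils or iron fails. The primary comparison stands if both lentil arms receive the same rice. The bias cannot be quantified from the article. This should be corrected because it changes what the secondary comparison and the growth question can conclude, but it does not threaten the trial's main result.

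**What to change.** Reconcile Trial objectives, Intervention, Data collection tools and technique, and Discussion:

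1. Name rice in the Intervention section, state which arms receive it, and specify the same portion in both lentil arms.
2. Label every contrast with usual intake, including those for growth and cognition, as the effect of the dal-and-rice meal package. Limit claims about iron or fortification to arm 1 against arm 2, as the Intervention section already implies. Bring the hypothesis and the Discussion's true-effect wording into line.
3. Add rice served and uneaten to the existing daily record, so that equality between the lentil arms can be checked.
4. Delete the statements that dal is the only intervention and that providing rice controls a covariate.

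The cost is wording, one extra entry on a form that research assistants already complete, and a narrower claim for the usual-intake contrasts. The article gives the trial status as not yet recruiting, so on its own account all four changes can still be made. If feeding has begun, the labelling and the deletions remain possible.

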### Trial status

Not yet recruiting.

## Abbreviations

AC: Adolescent Clubs
CDC: Crop Development Centre
DDS: Dietary Diversity Score
DPS: Department of Plant Sciences
DSMB: Data Safety Monitoring Board
FFQs: Food frequency questionnaires
GoB: Government of Bangladesh
icddr,b: International Centre for Diarrhoeal Disease Research, Bangladesh
LSBE: Life-skill-based education
NaFeEDTA: Sodium iron ethylenediaminetetraacetic acid
sFer: Serum ferritin
sTfR: Soluble transferrin receptor
TBI: Total body Fe
UID: Unique identifier number
UofS: University of Saskatchewan
VAS: Visual analog scale
